## Abstract

**Background:**

Tuberculosis (TB) poses a major public health challenge, particularly in children. A substantial proportion of children with TB disease remain undetected and unconfirmed. Therefore, there is an urgent need for a highly sensitive point-of-care test. This study aims to assess the performance of serological assays based on various antigen targets and antibody properties in distinguishing children (0–18 years) with TB disease (1) from healthy TB-exposed children, (2) children with non-TB lower respiratory tract infections, and (3) from children with TB infection.

**Methods:**

The study will use biobanked plasma samples collected from three prospective multicentric diagnostic observational studies: the Childhood TB in Switzerland (CITRUS) study, the Pediatric TB Research Network in Spain (pTBred), and the Procalcitonin guidance to reduce antibiotic treatment of lower respiratory tract infections in children and adolescents (ProPAED) study. Included are children diagnosed with TB disease or infection, healthy TB-exposed children, and sick children with non-TB lower respiratory tract infection. Serological multiplex assays will be performed to identify *M. tuberculosis* antigen-specific antibody features, including isotypes, subclasses, Fc receptor (FcR) binding, and IgG glycosylation.

**Discussion:**

The findings from this study will help to design serological assays for diagnosing TB disease in children. Importantly, those assays could easily be developed as low-cost point-of-care tests, thereby offering a potential solution for resource-constrained settings.

**ClinicalTrials.gov Identifier:**

NCT03044509.

**Supplementary Information:**

The online version contains supplementary material available at 10.1186/s12879-024-09359-0.

## Background

Diagnosing tuberculosis (TB) in children presents several challenges [1]. TB disease in children is confirmed only in about 50% of patients due to the paucibacillary nature [2, 3]. In the absence of a reliable and easily accessible diagnostic test for screening and confirming TB disease in children, diagnosis typically relies on clinical findings, TB contact history, chest radiography findings, and the results of immune-based TB tests, the Tuberculin skin test (TST) and interferon-γ release assays (IGRA) [4]. However, both immunodiagnostic tests have suboptimal performance and are not well-suited for screening for TB disease [5, 6].

Serological assays have the potential to serve as a screening tool for TB infection and disease in children, especially in resource-limited settings where advanced diagnostic methods are limited. This potential stems from their blood-based nature, thus not requiring sputum collection, and their feasibility to be used as point-of-care tests [7]. However, currently available commercial serological assays are not recommended for clinical use due to their insufficient and variable diagnostic performance, characterised by limited sensitivity, specificity, and susceptibility to cross-reactivity [8, 9]. In a recent narrative review focusing on the diagnostic performance of non-commercial serological assays for TB in children, we found that studies which measured antibodies against only one antigen generally reported relatively high specificity but only achieved limited sensitivity [10]. Higher sensitivity can be achieved when antibodies against multiple targets are measured, and results are interpreted in combination. In addition, emerging evidence suggests that certain antibody properties, such as antibody Fc receptor (FcR) binding profiles [11, 12] and antibody glycosylation patterns [13], can potentially be used to differentiate between TB infection and disease. However, most of those studies have been done in adults, and the evidence in children remains extremely limited.

## Methods

### Aim

The aim of this study is to evaluate the diagnostic performance of serological assays in detecting children with TB disease, and in distinguishing those subjects from (1) healthy TB-exposed children, (2) children with non-TB lower respiratory tract infection, and (3) children with TB infection.

### Study setting and population

This study will utilise plasma samples obtained from three different prospective multicentric observational studies: the Childhood Tuberculosis in Switzerland (CITRUS) study (NCT03044509), the Pediatric TB Research Network in Spain (pTBred), and the Procalcitonin guidance to reduce antibiotic treatment of lower respiratory tract infections in children and adolescents (ProPAED) study (ISRCTN 17,057,980) (Table 1).

**Table 1 Tab1:** Overview of studies from which samples will be used in the described project, including inclusion- and exclusion criteria

	Inclusion criteria	Exclusion criteria	Study design	Time	Country
CITRUS	< 18 years Undergoing evaluation for TB exposure, TB infection, TB disease	- Anti-mycobacterial treatment more than 5 days prior to inclusion - Previous treatment for TB disease or infection	Multi-centric study with nine centres in Switzerland	Since May 2017 (on going)	Switzerland
pTBred	< 18 years Undergoing evaluation for TB exposure, TB infection, TB disease	- Anti-mycobacterial treatment more than 5 days prior to inclusion - Previous treatment for TB disease or infection	Multidisciplinary collaborative network	Oct 2019 - Jun 2021	Spain
ProPAED	pulmonary non-TB disease: < 18 years, presentation with lower respiratory tract infection including fever and cough, regardless of previous antibiotic treatment history	- Severe immunosuppression - Known HIV infection - Immunosuppressive treatment - Neutropenia - *M. tuberculosis* infection - Cystic fibrosis - Viral laryngotracheitis - Hospital stay within the previous 14 days - Other severe infections (e.g., osteomyelitis, endocarditis, or deep tissue abscesses)	Multi-centric study with two emergency departments	Jan 2009 - Feb 2010	Switzerland

CITRUS is a multicentric prospective diagnostic study done at nine centres across Switzerland (Bern, Basel, Zurich, Lausanne, Geneva, Aarau, St. Gallen, Lucerne, Bellinzona). Its primary objective is to evaluate and validate novel immunodiagnostic assays for childhood TB [14, 15]. The study includes children under the age of 18 years, with or without a history of Bacillus Calmette-Guérin (BCG) vaccination, who are undergoing evaluation for TB disease, infection, and exposure. Children who have received any anti-mycobacterial treatment for five days or more before inclusion or who have been previously treated for TB disease or infection are excluded. Recruitment for the CITRUS study began in May 2017 and is currently ongoing.

PTBred is a multidisciplinary collaborative network established in 2014 in Spain, recruiting children < 18 years with TB. Since 2017, different types of samples have been stored in the Biobank of the Gregorio Marañon Hospital or in the individual collection registered as C.0006631 in the National Biobank Collections Registry. For this study, a common protocol for sample processing was implemented in October 2019, including children with children with TB disease, infection, and exposure irrespective of their BCG-vaccination status. The pTBred and CITRUS study follow the same inclusion and exclusion criteria [16].

The ProPAED study collected samples from children and adolescents presenting with fever and cough at two emergency departments in Switzerland (Basel and Aarau), from January 2009 to February 2010. For the ProPAED study, children with severe immunocompromise or known HIV infection, those undergoing immunosuppressive treatment, children with *M. tuberculosis* infection, neutropenia, cystic fibrosis, viral laryngotracheitis, hospital stay within the preceding 14 days, or other severe infections (e.g., osteomyelitis, endocarditis, or deep tissue abscesses) were excluded [17].

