### Case definitions

In this study, we will use the published criteria of compound TB case definitions proposed by Graham et al. [18]. Briefly, confirmed TB disease is defined as the presence of bacteriologically confirmed TB disease through culture or nucleic acid amplification tests (NAAT). Unconfirmed TB disease is defined as the absence of bacteriological confirmation in the presence of at least two of the following criteria: symptoms or signs suggestive of TB disease, chest radiograph consistent with TB disease, close TB exposure or immunologic evidence of *M. tuberculosis* infection, positive response to TB treatment. TB infection is defined as the presence of immunologic evidence of *M. tuberculosis* infection, including a positive TST of ≥ 5 mm (in accordance with the Swiss and Spanish guidelines [19, 20]) or a positive IGRA without meeting the criteria for confirmed or unconfirmed TB disease. Healthy TB-exposed children are defined as asymptomatic individuals with negative results on IGRA or TST test (single or repeat testing according to age, time since exposure as defined by national guidelines), making them unlikely to have TB. Children with non-TB lower respiratory tract infection will be the sick control group and are defined as presenting with fever (core body temperature ≥ 38.0° C) and at least one symptom (cough, sputum production, pleuritic pain, poor feeding) and at least one sign (tachypnea, dyspnoea, wheezing, late inspiratory crackles, bronchial breathing, pleural rub) lasting for fewer than 14 days.

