### Data analysis

Descriptive statistics, including mean, median, standard deviation, and interquartile range, will be used to summarise antibody concentrations stratified by diagnostic group (TB disease, TB infection, healthy TB-exposed controls, and non-TB lower respiratory tract infections) and age groups (< 2 years, 2 to < 5 years, 5 to < 10 years, and ≥ 10 years). Antigen-specific antibody concentrations will be analysed in relation to the total (nonspecific) antibody concentrations. Comparisons between groups will be made using t-tests or Mann-Whitney *U* tests if normality assumptions are not met. Children with TB disease and infection will be compared with the following groups: all other remaining children combined, healthy TB-exposed children, and children with non-TB lower respiratory tract infections.

To assess the performance of each individual antigen specific antibody feature as a diagnostic assay, sensitivity and specificity will be calculated based on cut-off values determined by the highest Youden’s index. Receiver operating characteristic (ROC) analysis will be performed, and area under the curve (AUC) will be calculated (confidence interval will be determined using the DeLong method).

In subsequent analyses, we aim to evaluate the combined interpretation of antigen-specific antibodies concentrations and properties using different strategies:

Strategy one involves defining cut-off values based on a specificity of ≥ 98%, in accordance with the minimal WHO’s target product profile(TPP) requirement for a biomarker-based detection test. We will calculate the corresponding sensitivity. Similarly, we will determine cut-off values based on a sensitivity of ≥ 66% and calculate the corresponding specificity. To assess the combined interpretation of multiple antigen targets, the test for a specific antibody or antibody property will be scored positive if at least one antibody level against a specific antigen exceeds the cut-off value in an individual’s plasma sample, and negative if all antibody levels against all antigens in a plasma sample are below the cut-off values.

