Another strategy for the combined interpretation of multiple antibody concentrations and properties will involve feature selection using the least absolute shrinkage and selection operator (LASSO). This approach will help identifying the most informative features that could be used in diagnostic assays. To validate the predictive power of the selected features (k features), we will train and evaluate an additional model using only those k features. In a further step, we will include the selection of antibody concentrations and properties in the training of the model. By performing feature selection using LASSO, we aim to maximize prediction performance using all features and select the k most informative features after the training stage. This procedure is based on the concept that selecting the most informative features from a well-performing prediction model will also yield a well-performing prediction model when one only has access to the selected subset of features. Recent advances in machine learning research will enable us to incorporate feature subset selection directly into the training step of a model [54, 55]. Therefore, we optimise not only the prediction performance but also the subset selection of k features during training. The choice of subset size, k, should be based on external constraints. The diverse sensitivities and specificities observed in paediatric TB serological tests make a precise sample size determination challenging. To estimate the sample size for our experiments, we used data generated from a cohort of adults with latent infection (*n* = 20) and active pulmonary disease (*n* = 22) from South Africa [56]. For the analysis of 75 antibody features, linear regression was conducted to assess the association between diagnosis and antibody feature, while controlling for age and gender. For the thirteen features exceeding a false discovery rate threshold of 10%, the partial correlation coefficient of 0.50 or higher was observed between diagnosis and antibody feature. Using this estimate as the effect size of biologically active antibody features, 68 individuals in an independent cohort (34 LTB, 34 ATB) would provide a statistical power of 80% to observe significant differences in top antibody features between tuberculosis infection and disease at an alpha level of 0.0005. This alpha level represents the threshold for significance required by the Bonferroni-Holm correction method, set at 0.0005 to accommodate the testing of 100 antibody features.

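### CITRUS and pTBred can enrol several children from one household, while the named tests and AUC intervals assume independent children

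*Protocol article*

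**What the plan says.** Under Study setting and population, CITRUS includes children under 18 "who are undergoing evaluation for TB disease, infection, and exposure". For the Spanish cohort the article states: "The pTBred and CITRUS study follow the same inclusion and exclusion criteria". The listed exclusions, in the text and in Table 1, concern treatment only: recent anti-mycobacterial therapy, and children "who have been previously treated for TB disease or infection are excluded". Households, siblings and shared index cases are not mentioned.

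Under Case definitions, contact with a TB case runs through the groups. One of the criteria for unconfirmed TB disease is "close TB exposure or immunologic evidence of" *M. tuberculosis* infection. The control group is set out as follows: "Healthy TB-exposed children are defined as asymptomatic individuals with negative results on IGRA or TST test".

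Under Data analysis, the methods are named: "Comparisons between groups will be made using t-tests or Mann-Whitney" *U* tests, and DeLong confidence intervals for the AUC. The LASSO strategy adds a further step, "we will train and evaluate an additional model using only those k features", without saying how data are divided for training and evaluation. The sample size, in the same section, is 68 individuals (34 with infection, 34 with disease) for 80% power at alpha 0.0005.

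**The concern.** When one infectious person is found, several children in the same home may be evaluated for exposure. Such children share the source case, the intensity of exposure and much of their background, any of which may shape antibody levels. The eligibility rules allow them all to enter, and the case definitions allow them to land in the same diagnostic group or in different ones.

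In standard form, the two-sample t-test, the Mann-Whitney test and the DeLong variance all assume independent subjects. If that fails, the reported p-values and interval widths do not carry their stated error rates. Siblings in the same group make standard errors too small. Siblings split across the compared groups make unpaired tests conservative. The AUC, sensitivity and specificity estimates are not the target of this argument; their intervals are.

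Two of the three comparisons in the Aim, disease versus healthy exposed and disease versus infection, rest on these two cohorts alone. There is a second, looser risk: if the LASSO models are evaluated on a random split of children, siblings could sit on both sides of it and make accuracy look better than it is.

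**Working it through.** **Plan's own figure.** Inputs from Data analysis: partial correlation 0.50, adjustment for age and gender (2 covariates), power 80%, alpha 0.0005. Two-sided testing is assumed, since the article does not state it. By Fisher's z:

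N = ((3.481 + 0.842) / atanh(0.50))² + 3 + 2 = (4.322 / 0.5493)² + 5 = 66.9, so 67.

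The stated 68 reproduces to within one child, and power at 68 is 81.0%. The calculation is sound, and it counts every child as one independent observation (design effect 1).

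**Illustration of same-group siblings.** The article gives neither household sizes nor an intra-household correlation (ICC), so the following inputs are assumptions.

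- Households in one group contribute 1, 2 or 3 children in shares 60%, 25% and 15%.
- Mean per household: 0.60×1 + 0.25×2 + 0.15×3 = 1.55.
- Size-weighted mean: (0.60×1 + 0.25×4 + 0.15×9) / 1.55 = 2.95 / 1.55 = 1.90. This is the mean that enters the design effect.
- ICC = 0.3. Design effect for that group: 1 + (1.90 − 1) × 0.3 = 1.27.
- With equal group sizes, equal variances and no clustering in the other group, the factor for the variance of the difference is (1.27 + 1) / 2 = 1.135, or about 1.13.

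True two-sided error = 2 × (1 − Φ(z / √factor)), with the factor at 1.13:

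| Nominal level | z | z / √1.13 | True error |
|---|---|---|---|
| 0.0005 | 3.481 | 3.27 | 0.00106 |
| 0.05 | 1.960 | 1.84 | 6.5% |

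These shares are not mild. They imply that 1 − 0.60/1.55 = 61% of the children in that group have a sibling enrolled in the same group.

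**Range.** Using 1 + (m − 1) × ICC with every sibling in the same group, on both sides of the comparison, m from 1.2 to 2.5 and ICC from 0.1 to 0.5 give design effects of 1.02 to 1.75. The equivalent of 68 independent children is then 70 to 119 children. Nothing in the article places the study within this range, or rules out a design effect of 1.

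**Illustration of split siblings.** If half the children are paired with a sibling in the opposite group and ICC = 0.3, the variance factor is 1 − 0.5 × 0.3 = 0.85. The unpaired test is then conservative: the true error at nominal 0.05 is 2 × (1 − Φ(1.960 / √0.85)) = 3.4%.

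**The case against.** The strongest reply is that siblings are an inference. The article never mentions siblings or households. It does not describe how children were referred or how biobanked samples were chosen for this work, and the enrolment detail sits in the parent studies. A condensed article also commonly names a test without its variance option. It is fair that frequency, correlation and direction are all unknown, and no figure in the article is wrong. What remains is that the article names specific methods that need independent children, under eligibility rules that do not secure it.

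Three stronger readings are tempting and are not supported.

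- *Every model fit ignores households.* The article does not describe folds, a hold-out set or a resampling unit for LASSO. Leakage between siblings is a risk to guard against, not a stated error, and the split may be settled in a fuller plan.
- *The whole study is affected.* ProPAED children came to emergency departments with fever and cough, so recruitment through a shared TB index case does not apply to that control group.
- *The error at 0.0005 is several times larger.* A 4.5-fold excess needs a variance factor of 1.3. With one clustered group, equal group sizes and ICC 0.3, that requires a group design effect of 1.6 and hence a size-weighted cluster of 3.0. The illustration supports about a twofold excess, and only if siblings fall in the same group.

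**Conclusion.** The point stands as a low-cost improvement, not as a demonstrated error. The stated eligibility for CITRUS and pTBred does not prevent related children from entering, and the group tests and DeLong intervals named for them assume independence. Under the stated assumptions (one group clustered, 61% of its children with a same-group sibling, ICC 0.3), the true error is about double the nominal 0.0005 and about 6.5% at nominal 0.05. If siblings are mostly split between compared groups, the tests are conservative instead. If there are none, the plan is unaffected. A reader might infer that the sample size of 68 is wrong; it is not, since it reproduces, and it only lacks an allowance whose size the article gives no means of setting.

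**What to change.** - Where the link can be retrieved, attach a household or index-case identifier to each CITRUS and pTBred sample. CITRUS is still recruiting, so new enrolments can carry it from the start.
- Count the households contributing more than one child, within and across diagnostic groups. If there are none, say so; no further change is needed.
- If there are some, use household-clustered standard errors or a bootstrap that resamples households for the group comparisons, and likewise for AUC, sensitivity and specificity intervals. Both handle same-group and split siblings.
- Keep all members of a household in the same fold or data set for LASSO training and evaluation.
- Report a sensitivity analysis with one child per household.

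The cost is the work of retrieving links, which may not be possible for every stored sample, and possibly slightly wider intervals. No new samples or assays are needed.

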### Case definitions

In this study, we will use the published criteria of compound TB case definitions proposed by Graham et al. [18]. Briefly, confirmed TB disease is defined as the presence of bacteriologically confirmed TB disease through culture or nucleic acid amplification tests (NAAT). Unconfirmed TB disease is defined as the absence of bacteriological confirmation in the presence of at least two of the following criteria: symptoms or signs suggestive of TB disease, chest radiograph consistent with TB disease, close TB exposure or immunologic evidence of *M. tuberculosis* infection, positive response to TB treatment. TB infection is defined as the presence of immunologic evidence of *M. tuberculosis* infection, including a positive TST of ≥ 5 mm (in accordance with the Swiss and Spanish guidelines [19, 20]) or a positive IGRA without meeting the criteria for confirmed or unconfirmed TB disease. Healthy TB-exposed children are defined as asymptomatic individuals with negative results on IGRA or TST test (single or repeat testing according to age, time since exposure as defined by national guidelines), making them unlikely to have TB. Children with non-TB lower respiratory tract infection will be the sick control group and are defined as presenting with fever (core body temperature ≥ 38.0° C) and at least one symptom (cough, sputum production, pleuritic pain, poor feeding) and at least one sign (tachypnea, dyspnoea, wheezing, late inspiratory crackles, bronchial breathing, pleural rub) lasting for fewer than 14 days.

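### In the disease-versus-LRTI contrast, diagnostic group and source cohort are the same variable, so its diagnostic accuracy cannot be separated from cohort effects

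*Protocol article*

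**What the plan says.** Under Case definitions, "Children with non-TB lower respiratory tract infection will be the sick control group", defined by fever plus at least one symptom and one sign for under 14 days. That definition names no cohort, but Table 1 does: ProPAED is the only source study entered for "pulmonary non-TB disease: < 18 years, presentation with lower respiratory tract infection including fever and cough". It recruited "at two emergency departments in Switzerland (Basel and Aarau), from January 2009 to February 2010". Its exclusions include known HIV infection, severe immunosuppression, immunosuppressive treatment, neutropenia and *M. tuberculosis* infection, so it supplies no cases.

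The other two studies supply TB disease, infection and exposure. CITRUS takes children "who are undergoing evaluation for TB disease, infection, and exposure", and "Recruitment for the CITRUS study began in May 2017 and is currently ongoing". For pTBred, "a common protocol for sample processing was implemented in October 2019", and Table 1 dates its samples October 2019 to June 2021. Both list only two exclusions, one on prior anti-mycobacterial treatment and one on previous treatment for TB disease or infection.

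The Data analysis section compares children with TB disease and infection with "all other remaining children combined", with healthy TB-exposed children and with the LRTI group. It relates antigen-specific to total antibody. The section on antigens and antibody properties adds totals per isotype and per Fc receptor for quality control and possible normalisation. No term for cohort, site or storage time is described.

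**The concern.** The second aim is the only one that sets children with TB disease against children who are ill with something else, so it lies closest to how a diagnostic test would be used. If every sick control comes from one cohort and every case from others, any systematic difference between cohorts appears as diagnostic accuracy. Sampling era, setting, eligibility, background exposure or sample handling could each cause one. Sensitivity, specificity and AUC for this contrast would then describe a mixture of disease and cohort. A later analysis plan cannot repair this by adjustment, because the data hold no information with which to separate the two.

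**Working it through.** **1. Cohort by group** (Table 1, Study setting and population, Case definitions)

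| Group | CITRUS | pTBred | ProPAED |
|---|---|---|---|
| TB disease | yes | yes | no |
| TB infection | yes | yes | no |
| Healthy exposed | yes | yes | no |
| Non-TB LRTI | none described | none described | yes |

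An intercept, three group indicators and two cohort indicators make 6 columns, but the matrix has rank 5: the LRTI column equals the ProPAED column. Disease versus LRTI is completely aliased with cohort. Disease versus infection and disease versus healthy exposed lie within CITRUS/pTBred and remain estimable with a cohort term.

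**2. Time gap.** February 2010 to May 2017 is 7 × 12 + 3 = 87 months. To October 2019, the pTBred start, it is 9 × 12 + 8 = 116 months.

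**3. Effect on a marker with no TB signal.** Assume normal values, equal variances and a pure cohort shift of s SD. Then AUC = Φ(s/√2):
- s = 0.2: Φ(0.141) = 0.56
- s = 0.5: Φ(0.354) = 0.64
- s = 1.0: Φ(0.707) = 0.76

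The shifts are assumptions; the documents give none.

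**4. How many features could be affected.** The plan's only sample-size figure is 68 (34 + 34), for infection versus disease. It reproduces by Fisher's z, two-sided, with two covariates: ((3.481 + 0.842)/0.549)² + 3 + 2 = 66.9, so 67, or 68 when split evenly. Borrowing 34 per group and alpha 0.0005 purely for illustration, a two-sample t-test would flag about 0.4, 6.5 and 67 of 100 features with no TB signal at s = 0.2, 0.5 and 1.0.

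**5. Pooled contrast.** If ProPAED makes up a share w of the comparator, the AUC of such a marker is w·Φ(s/√2) + (1 − w)·0.5. The article does not give w. At s = 0.5, w = 0.25, 0.50 and 0.75 give 0.53, 0.57 and 0.60.

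**6. Is a cohort-matched sick control available?** Unconfirmed TB needs two of four criteria: symptoms, radiograph, exposure or immunologic evidence, and treatment response. A symptomatic CITRUS/pTBred child without close exposure, with negative TST/IGRA and neither of the other two criteria, meets one. That child is not TB disease, not TB infection (no immunologic evidence) and not healthy exposed (symptomatic). Unless the acute febrile LRTI definition is met, the child has no group. The number of such children is not stated.

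**The case against.** The strongest reply is that the plan has safeguards. Samples are stored at −80 °C, and totals per isotype and per Fc receptor are planned as possible normalisers. A reader might infer that Fc-receptor signals have no normaliser; the article shows otherwise. This stands for general storage loss. It does not reach differences in site, eligibility, exposure background or handling.

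The other contrasts also give a partial check: a feature that separates disease from LRTI but not from healthy exposed children would be suspect. That stands too, although it does not identify the cohort effect. Basel and Aarau are CITRUS centres as well, which brings place closer but not era or eligibility.

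Some stronger readings are not supported:
- **That LASSO will learn the cohort.** The pooled comparator is specified for the group comparisons, and the LASSO text names no negative class. The risk is conditional.
- **That combining shifted features drives the AUC towards 1.** Ten independent features at 0.5 SD would give Φ(0.5·√10/√2) = 0.87. With an assumed common correlation of 0.5 and any number of equally shifted features, however, the distance is at most s·√2, so the AUC is at most Φ(s): 0.58, 0.69 and 0.84 for s = 0.2, 0.5 and 1.0.
- **That all symptomatic children in whom TB is ruled out are ungrouped.** Symptoms plus close exposure or a positive TST/IGRA already make unconfirmed TB, and an acute febrile LRTI could literally meet the sick-control definition. Only the narrower subgroup in the working is left out, and the article condenses published case definitions.
- **That groups will sit on separate assay plates.** The article is silent on plate layout, which is laboratory detail commonly left out.

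**Conclusion.** The point holds for disease versus LRTI, where group and cohort are fully aliased, and partly for the pooled comparison. It does not touch disease versus infection, disease versus healthy exposed, or the sample size. That the LRTI group is ProPAED only follows from Table 1 and the groups the other studies are said to supply; the case definition does not say so outright.

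The aliasing is a matter of design and needs no assumption. Its consequence does: 0.56, 0.64 or 0.76 for a marker with no TB signal rests on an assumed shift of 0.2, 0.5 or 1.0 SD, and the true shift could be negligible. The defect is that the planned data cannot show which, and the article does not acknowledge it. The plan should be changed before cut-offs and models are fitted, but the second aim need not be abandoned.

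**What to change.** - Derive cut-offs and any multi-feature model from the contrasts within CITRUS/pTBred, then apply them locked to ProPAED as an external specificity check.
- Report the pooled comparison with and without ProPAED.
- In the ProPAED contrast, apply its HIV and immunosuppression exclusions to the cases as well.
- State that disease-versus-LRTI results are confounded with cohort.
- Where banked CITRUS/pTBred samples exist from symptomatic children evaluated for TB who meet neither the disease nor the infection definition (no close exposure, negative TST/IGRA), report them as a supplementary cohort-matched sick-control group. Making them the main comparison would rewrite the second aim.

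The first four are changes of wording and analysis; the last means assaying further samples. The costs are that cut-offs are not optimised for LRTI discrimination, a few cases may drop out of that contrast, and the supplementary group may be small. Locking stops the analysis from tuning to a cohort difference but does not remove it. A cut-off with 98% specificity (z = 2.054) would read Φ(2.054 + 0.5) = 99.5% or Φ(2.054 − 0.5) = 94.0% in ProPAED under an assumed 0.5 SD shift down or up, so the caveat is needed even with the other changes.
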